### Participants

#### Inclusion criteria

Any adult (≥18 years) patient with a known diagnosis of T2DM according to the primary care record in the Hampshire, Wiltshire, Dorset and the Isle of Wight (all UK) areas will potentially be eligible to participate. Non-English-speaking patients will be eligible for inclusion.

#### Exclusion criteria

<18 years of age.Evaluated for liver disease with either an ELF test or VCTE in the 2 years before the date of consent.A known prior clinical diagnosis of significant liver disease (significant fibrosis or cirrhosis and in active hospital follow-up) due to any cause.A known diagnosis of autoimmune hepatitis, primary biliary cholangitis and primary sclerosing cholangitis or viral hepatitis (irrespective of whether this has progressed to fibrosis or cirrhosis).

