### Primary outcome

The number of participants referred to secondary care with the suspected liver disease within 12 months of randomisation who are subsequently referred for HCC surveillance.

As an unblinded trial, it is important our primary outcome is as objective as possible and independent of the research team. In both study arms, patients with high liver stiffness measurements will be referred to nearby hepatology services (with thresholds defined by local practice). Via usual care, an independent local clinician will then assess the severity of liver disease. In real-world practice, this may include history, examination, no further tests or repeat VCTE, additional tests for fibrosis and in some cases liver biopsy. Regardless of the clinical approach taken, the primary outcome will be whether the clinician felt the disease was severe enough to warrant referral for HCC surveillance. Since the trial sites cover a variety of different regions across the south of England, this pragmatic approach is likely to closely reflect current UK practice.

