### Participant identification

Primary care centres will identify potential participants from their patient records. The research team will provide these practices with a search query to run on their patient management systems (SystmOne or EMIS) (see online supplemental material and trial website (reflexstudy.org)). Flagged patients will be screened for eligibility by practice staff. The patients on the list of potential participants will be sent a text advising them about the study, where they can access further information and who to contact if they would like to self-refer their interest in participating (see online supplemental materials).

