### Arm 2—standard care—NICE guidelines based T2DM + additional risk factor testing

Participants in the standard care arm will not be contacted for VCTE, and following baseline data collection will have no further contact with the research team during the follow-up period—outcomes will be collected remotely from the medical record (see below).

Standard care varies across the study area but is based on 2016 NICE guidance (NG49) (figure 1).^32^ In the 2016 NICE NAFLD guideline, the presence of T2DM does not trigger an assessment for liver disease in the absence of other specific risk factors.^32^ ‘Risk factors’ to enter standard care vary in the study areas but broadly include harmful alcohol consumption, an elevated ALT and a fatty liver on ultrasound examination. If risk factor thresholds are met, then the usual care pathway varies further, but in all areas involve VCTE with or without a biomarker for liver fibrosis (eg FIB-4 or ELF) (figure 1). The variation in standard care is very important as it increases the external validity of our study by being representative of the heterogeneity across the UK.

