#### Primary outcome data collection

The primary outcome—referral to HCC surveillance following a referral with suspected liver disease from primary care will be assessed by the research team from each participant’s healthcare records. Participants will not need to be recontacted for outcome data. For standard care participants, the primary care record will be reviewed for a referral letter to secondary care or a community liver assessment service that was sent within 12 months of randomisation. For both trial arms, records will be reviewed for evidence (eg a letter from hepatology services) that the patient has been enrolled in HCC surveillance. The primary care record review will take place up to 30 months from randomisation to ensure enough time for definitive decisions regarding HCC surveillance to have been made by the clinical team.

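### Patients with an open liver referral can be randomised, and the referral-date rule, stated for standard care only, can drop them from the control count while the screening arm keeps them

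*Protocol article*

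**What the plan says.** **Eligibility.** Under Exclusion criteria, recent testing is handled by "Evaluated for liver disease with either an ELF test or VCTE in the 2 years before the date of consent", and existing disease by "A known prior clinical diagnosis of significant liver disease (significant fibrosis or cirrhosis and in active hospital follow-up) due to any cause". A further item names specific liver diagnoses. None mentions a referral or test request that is still open. Under Participant identification, "Flagged patients will be screened for eligibility by practice staff"; the search query itself is in a supplement.

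**Outcome.** The Primary outcome section defines it, without distinguishing the arms, as "The number of participants referred to secondary care with the suspected liver disease within 12 months of randomisation who are subsequently referred for HCC surveillance". It adds that a high stiffness reading leads to hepatology referral in either arm.

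**Ascertainment.** Primary outcome data collection says that, for standard care participants, the record is searched for "a referral letter to secondary care or a community liver assessment service that was sent within 12 months of randomisation". The next sentence covers everyone: "For both trial arms, records will be reviewed for evidence (eg a letter from hepatology services) that the patient has been enrolled in HCC surveillance". Thus a letter-date check is stated for standard care alone.

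**Routes to testing.** In Arm 1 the research team refers every participant for VCTE and blood tests after randomisation. In Arm 2 the local pathways "in all areas involve VCTE with or without a biomarker for liver fibrosis (eg FIB-4 or ELF").

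**The concern.** Consider a patient whose GP found a raised ALT or harmful drinking, perhaps with a raised FIB-4, and sent a liver referral a few weeks before consent. No ELF or VCTE has been done and no diagnosis made, so no exclusion applies.

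Randomisation balances the number of such patients between arms, so this is not confounding. The problem is that the two arms may count them differently. In standard care, the letter that led to the diagnosis may be too early to qualify. In the screening arm, the same patient gets a new assessment route that starts after randomisation.

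The trial asks what universal screening adds to usual care. A case that usual care had already picked up at entry should not be lost from one arm and credited to the other. The Data analysis section expects so few events that it plans exact or penalised estimation, so one or two misplaced control events could be visible. The trial's findings also feed the usual-care strategy in the economic model.

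**Working it through.** **1. Who is affected.** Setting the passages side by side:

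- *Control sent directly to secondary care before randomisation, no later letter.* Not excluded. The letter falls outside the natural reading of the 12-month window, so this can be a non-event even if surveillance follows.
- *Control awaiting community VCTE, referred before randomisation.* Not excluded. If stiffness is high, a hepatology letter should follow after randomisation and could qualify. However, the data collection section frames the outcome as following a referral from primary care and accepts a community-service letter as that referral. If only the primary care letter counts, this case is lost too.
- *Either patient in the screening arm.* Referred for VCTE after randomisation, with no letter-date check stated, so can count.
- *Patient who already had ELF before referral.* Excluded already.

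**2. The plan's own figures.** The plan gives 320 per arm, with at least 80% power at 25% drop-out (320 × 0.75 = 240) and more than 90% at 5% (320 × 0.95 = 304). The event rates are in Figure 3, which is not shown, and the text gives no alpha, so the power cannot be reproduced. This point changes no stated figure.

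**3. Control events missed.** Formula: 320 × w × y × s. All three inputs are assumptions, because the text gives none of them:

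- w, share already referred and waiting at consent: 0.5% to 3%
- y, share of those who reach HCC surveillance: 5% to 20%
- s, share of waiting controls with no new qualifying letter: 25% to 100%

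Lowest: 320 × 0.005 × 0.05 × 0.25 = 0.02. Highest: 320 × 0.03 × 0.20 × 1.00 = 1.92.

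The highest value implies a loss of 0.6 percentage points (0.03 × 0.20), so it is possible only if the true control rate is at least 0.6%.

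**4. Effect on the comparison.** Counted control rate = true control rate − w × y × s; the screening rate is unchanged. The true rates are also assumed.

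| True control / screening | w, y, s | Missed per 320 | Counted control rate | Risk difference (points) | Risk ratio |
|---|---|---|---|---|---|
| 0.5% / 4% | 0.5%, 5%, 50% | 0.04 | 0.49% | 3.5 → 3.51 | 8.0 → 8.2 |
| 0.5% / 4% | 1%, 10%, 100% | 0.32 | 0.40% | 3.5 → 3.6 | 8.0 → 10.0 |
| 0.5% / 4% | 2%, 20%, 50% | 0.64 | 0.30% | 3.5 → 3.7 | 8.0 → 13.3 |
| 1% / 5% | 1%, 10%, 100% | 0.32 | 0.90% | 4.0 → 4.1 | 5.0 → 5.6 |
| 1% / 5% | 2%, 20%, 50% | 0.64 | 0.80% | 4.0 → 4.2 | 5.0 → 6.25 |

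The risk difference moves by 0.2 points or less in these rows. The ratio moves more because its denominator rests on so few events: 320 × 0.005 = 1.6, or 320 × 0.01 = 3.2.

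**The case against.** **Onward letters.** The strongest objection is that the loss is not general. A control waiting for community VCTE who has a high reading should be referred to hepatology after randomisation, and that letter can qualify. The Abstract also words the outcome as surveillance referral following testing within 12 months of randomisation, which would count a post-randomisation test whatever the date of the first letter. This stands in large part. It limits the clear loss to controls whose only letter predates randomisation, and leaves the community group dependent on how the assessor reads the rule. That these wordings give different answers for the same patient is a reason to settle on one rule.

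**Screening-arm credit.** The outcome definition covers both arms, so a screening participant who already has a hepatology referral might generate no new one. This also stands: the text allows the case to count but does not establish that it always would.

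**Unseen material.** The search query or the practice check might already remove open referrals, and pathways that use ELF first shrink the pool. Both are possible, but the stated criteria require neither check.

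**Stronger readings to avoid.** A reader might infer that usual care gets no credit for any pending case. With a control rate of 0.5%, a six-month wait and a 3% screening rate, the pending pool is 6/12 × 0.5% = 0.25%. The odds ratio is then (0.03/0.97)/(0.005/0.995) = 6.15 as counted, against (0.03/0.97)/(0.0075/0.9925) = 4.09 with pending cases counted in both arms. That assumes every pending control is lost, which the onward-letter route contradicts, and every input is assumed. The risk difference in the same example moves by only 0.25 points. A reader might also suppose that waiting patients are more likely to answer the invitation text. Nothing in the article supports that, and they might equally decline because a scan is already arranged.

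**Conclusion.** The point holds in a limited form. As written, the exclusions admit patients with an open liver referral, and the letter-date check is stated for standard care only. A control whose only letter predates randomisation can be missed, while the same patient in the screening arm can be counted. Where the rule bites, the error favours screening.

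Its size cannot be determined from the article. Under the assumed ranges it is roughly 0 to 2 control events per 320, and it approaches zero if waiting controls receive qualifying onward letters. The risk difference is little affected. A ratio could shift materially if control events number only a few. The article does not support calling this a large bias, but it is worth closing because the outcome is rare, the assessment is unblinded and the remedy is cheap.

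**What to change.** 1. **Anyone still to be recruited:** add to the exclusions an open referral or request for liver fibrosis assessment or hepatology at the date of consent, checked by practice staff in the eligibility review they already do. The Setting section has recruitment complete by April 2025, so this helps only while recruitment is open.
2. **Anyone already randomised:** use the baseline primary care record to flag liver referrals dated before randomisation, identically in both arms and without reference to allocation or outcome.
3. **One dating rule for both arms:** for example, count any referral for HCC surveillance that follows a test or hepatology referral made within the 12 months after randomisation, whatever the date of the first letter. The Primary outcome section allows a hepatology assessment with no further tests, so the rule should also say whether such a visit counts for a patient referred earlier. Align the Abstract, Primary outcome and Primary outcome data collection wording with the rule.
4. **Analysis:** keep the primary analysis on all randomised participants, as the Data analysis section commits to, and pre-specify a sensitivity analysis without flagged participants. The flag is a pre-randomisation characteristic, so removing flagged participants from both arms keeps the comparison randomised.

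The cost is a handful of exclusions at most and one extra field in a record review that is already planned.

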### Setting

The study will be conducted in 16–20 primary care practices and diabetes community care hubs in Wessex (including Hampshire, Wiltshire, the Isle of Wight and Dorset (UK)). The setting of the study is important as it includes a range of existing community liver pathways which means the intervention is compared with a diverse representation of standard care—which is a representative of diverse interpretations of the current NICE guidelines.^32^

Community hubs will be used for research data collection including VCTE and blood sampling. Primary care centres will be identified via the local Primary Care Network and the Primary Care NIHR clinical research network. The number of practices we are using is justified in the later dedicated sections of the form.

Recruitment will take place from January 2024 and will be complete by April 2025. Outcome data collection will be completed by June 2026, and the cost-effective analysis will be completed by the study end date of 1 September 2026.

### Participant identification

Primary care centres will identify potential participants from their patient records. The research team will provide these practices with a search query to run on their patient management systems (SystmOne or EMIS) (see online supplemental material and trial website (reflexstudy.org)). Flagged patients will be screened for eligibility by practice staff. The patients on the list of potential participants will be sent a text advising them about the study, where they can access further information and who to contact if they would like to self-refer their interest in participating (see online supplemental materials).

### Consent and randomisation

If a participant contacts the research team, they will be sent an information sheet and given time to consider participation before providing written consent to the research team (see online supplemental material). After giving consent, each participant will be randomised. To ensure equal numbers of patients within each arm of the study, we will use block randomisation with a block size of 4. Blocks will be used to ensure a balance between the participants in each arm of the study—strata will be sex, age group and alcohol consumption. This will be managed by the Southampton NIHR Biomedical Research Centre team using randomisation software.^39^

### Arm 1—screening

Participants in this arm will be referred by the research team directly for liver fibrosis assessment at a community hub. This assessment will include VCTE and venepuncture for an ELF test and a FIB-4 index. The result of the VCTE and any abnormalities identified in the blood tests will be managed by the local liver disease care pathway (as per the usual care arm described below). VCTE will be performed by an experienced single operator after a minimum of a 3-hour fast and previously published criteria for a valid reading will be applied to each participant.^40^

### Arm 2—standard care—NICE guidelines based T2DM + additional risk factor testing

Participants in the standard care arm will not be contacted for VCTE, and following baseline data collection will have no further contact with the research team during the follow-up period—outcomes will be collected remotely from the medical record (see below).

Standard care varies across the study area but is based on 2016 NICE guidance (NG49) (figure 1).^32^ In the 2016 NICE NAFLD guideline, the presence of T2DM does not trigger an assessment for liver disease in the absence of other specific risk factors.^32^ ‘Risk factors’ to enter standard care vary in the study areas but broadly include harmful alcohol consumption, an elevated ALT and a fatty liver on ultrasound examination. If risk factor thresholds are met, then the usual care pathway varies further, but in all areas involve VCTE with or without a biomarker for liver fibrosis (eg FIB-4 or ELF) (figure 1). The variation in standard care is very important as it increases the external validity of our study by being representative of the heterogeneity across the UK.

**Figure 1 F1:**
[figure not shown]
An overview of usual care for liver disease assessment and management within primary and secondary care liver services in study areas—highlighting the complexities and subtle variations in practice. ALT, alanine transaminase; ELF, enhanced liver fibrosis; ETOH, alcohol; FIB4, fibrosis-4; LFT, liver function test; VCTE, vibration-controlled transient elastography.

After discussion with our patient and public involvement (PPI) groups, participants included in the standard care arm will be given the opportunity to undergo VCTE and a biomarker test to assess them for liver fibrosis >12 months following randomisation (arranged at mutual convenience with the research team).

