**Methods and analysis:**

The study will use a multi-centre, unblinded individual randomised controlled trial design. The aim will be to determine the effectiveness and cost-effectiveness of screening all adults with T2DM to identify those at high risk of HCC. The recruitment strategy has been supported by patient and public involvement (PPI). Participants will be identified via an automated search of primary care records and invited to participate via text. 320 participants will be randomised for screening. The screening will include measurement of bio-markers for liver fibrosis (ELF and Fib-4) and vibration-controlled transient elastography. Another 320 participants will be randomised to standard care. Demographic and medical history data will be collected at baseline from all participants. Outcome data will be collected remotely from healthcare records. The primary outcome is the proportion of participants in each arm who are referred to HCC surveillance following testing for liver disease within 12 months of randomisation. The results will be used to calculate the incremental cost-effectiveness ratio of screening via a Markov model.

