### Patient and public involvement

To design the trial, we have worked with two PPI representatives (one as PPI lead) and two PPI groups. Our PPI group was struck by the risk of liver cancer in people with diabetes. This was not something they were previously aware of. Both groups of contributors shared the views that cancer and specifically surveillance for liver cancer should be the focus of our research. Our groups are diverse—eight participants in total; two female; two non-white British; and one born in Eastern Europe. The PPI groups have helped develop our study recruitment strategy and our participant-facing study materials. Both groups raised some concerns about the use of a control arm. They advised us to ensure liver assessment was offered to all participants at the end of the study, and this has been incorporated into our study procedures.

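### A control referred by month 12 who enters HCC surveillance because of the study's own deferred VCTE can be counted as a usual-care event

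*Protocol article*

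**What the plan says.** All places are in the protocol article.

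- **Primary outcome.** It counts participants referred to secondary care "with the suspected liver disease within 12 months of randomisation who are subsequently referred for HCC surveillance". There are two steps: a referral by month 12, and a later surveillance referral with no date limit of its own.
- **Primary outcome data collection.** For controls the first step is a "referral letter to secondary care or a community liver assessment service that was sent within 12 months of randomisation". The second step is common to both arms: "For both trial arms, records will be reviewed for evidence (eg a letter from hepatology services) that the patient has been enrolled in HCC surveillance". On timing, "The primary care record review will take place up to 30 months from randomisation", so that clinicians have had time to decide.
- **Abstract (Methods and analysis).** It words the outcome as the proportion "referred to HCC surveillance following testing for liver disease within 12 months of randomisation".
- **Arm 2, text after Figure 1.** Controls "will be given the opportunity to undergo VCTE and a biomarker test to assess them for liver fibrosis >12 months following randomisation", arranged with the research team. No latest date is given.
- **Patient and public involvement.** The same offer is described differently: "They advised us to ensure liver assessment was offered to all participants at the end of the study".
- **Data analysis, Primary outcome.** Exact or penalised methods are planned because few events are expected.

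**The concern.** The control arm should show what usual care delivers by itself. The protocol protects it by keeping the research team away from controls during the 12-month follow-up, and the sample size allows for a doubling of background testing. That allowance is attributed to the Hawthorne effect, not to tests the study itself supplies. The protection ends at month 12, when the second step of the outcome may still be undecided.

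Two cases show the gap.

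- A control is referred in month 5, does not attend, has a high study VCTE in month 14, is referred again and enters surveillance.
- A control is sent to a community liver service in month 11, has had no VCTE there, and is assessed with the study result already in hand.

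Both have a letter by month 12 and later enrolment, so both satisfy the written rule. Only controls get the deferred test, so such events can only raise the control count and pull the comparison towards no difference. Analysis by randomised group does not remove this. The economic model also takes drop-out from the usual-care pathway as an input, and a non-attender brought back by the study test would look like someone who completed usual care.

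**Working it through.** **1. Does the overlap exist?** Under Setting, recruitment runs from January 2024 to April 2025 and outcome collection ends by June 2026.
- First recruit: month 12 is January 2025, leaving about 17 months to June 2026.
- Last recruit: month 12 is April 2026, leaving about 2 months.

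So there is overlap for everyone, but it is short for late recruits.

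**2. Who can be misattributed?**

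| Control's history | Meets the written rule? |
|---|---|
| No letter by month 12, first referred after a study test | No: first step fails |
| Letter by month 12, surveillance decided before any study test | Yes, correctly |
| Letter by month 12, no surveillance yet, enrolled after a study test | Yes, whichever test led to it |

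Only the third row is a problem.

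**3. The plan's power figure.** The article states at least 80% power at 25% drop-out and above 90% at 5%, with 320 per arm. The text shown gives no event rates or alpha, so this can only be checked for plausibility. Assume two-sided alpha 0.05 and

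power = Φ{ [ |p1−p2|√n − 1.96√(2p̄(1−p̄)) ] / √( p1(1−p1) + p2(1−p2) ) }.

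With 5% v 0.5%:
- n = 320 × 0.75 = 240: (0.6971 − 0.4533)/0.2291 = 1.06, power 86%.
- n = 320 × 0.95 = 304: power 93%.

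These rates fit the stated power. 5% v 1% would not (73% and 83%).

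**4. Size under the written rule.** Assume a screening rate of 4.75% (5% × 0.95) and a control rate of 0.5%. That is 15.2 and 1.6 expected events at n = 320, with power 92%. Let r be the share of controls with a letter by month 12, u the uptake of the study test, and q the chance that a tested control in this group then enters surveillance. None of these is in the document.

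Extra control events = 320 × (r − 0.005) × u × q

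| r | u | q | Extra events | Power |
|---|---|---|---|---|
| 1% | 25% | 5% | 0.02 | 92% |
| 1% | 50% | 5% | 0.04 | 92% |
| 5% | 50% | 20% | 1.44 | 82.5% |
| 5% | 75% | 20% | 2.16 | 76% |

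The result depends on r. At r = 10%, u = 75% and q = 20% it would be 4.56 events and 51% power, but that combines three high assumptions.

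**5. What one event can do.** Two-sided Fisher tests, 320 per arm, control v screening events:
- Verdict changes: 1 v 8 (p = 0.038) to 2 v 8 (0.107); 1 v 9 (0.021) to 2 v 9 (0.063); 2 v 10 (0.037) to 3 v 10 (0.089).
- Verdict unchanged: 1 v 10 (0.011) to 2 v 10 (0.037); 1 v 12 (0.003) to 2 v 12 (0.012); 2 v 15 (0.002) to 3 v 15 (0.007).

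The first group lies at the edge of 0.05; these pairs are illustrations, not expected results. Summing binomial probabilities over all outcomes in which adding one control event moves Fisher p from 0.05 or below to above 0.05 gives about 3% of trials at 0.25% v 5% and about 15% at 0.5% v 3.75%.

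**The case against.** The best defence is that the outcome reads naturally as one chain: referral, assessment by an independent clinician, surveillance decision. On that reading a second referral prompted by the study test does not belong to the chain. This is probably what was intended, but the text gives only an order in time, and the data-collection step asks only whether enrolment occurred.

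Second, controls waiting for hepatology will usually already have a high usual-care VCTE, because in all areas the standard pathway includes VCTE and high stiffness is what triggers the hepatology referral. A study VCTE then largely repeats what was known. This stands. It leaves mainly non-attenders and people sent to a community liver service but not yet scanned.

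Third, the two statements of when the test is offered may be compatible, since the article elsewhere treats follow-up as 12 months long. That is possible. But if the study's end means closure of outcome collection, the overlap largely disappears, so the difference matters.

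Fourth, a full protocol may contain an attribution rule. If so, it need only be confirmed. The article nevertheless states both the outcome rule and the offer, and together they leave the gap.

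A reader might infer something stronger: that the outcome stays open to month 30 for every control, so that any positive deferred test becomes a usual-care event. On the assumptions above with 5% positivity, uptake of 25%, 50% or 75% would then add about 4, 8 or 12 control events and cut power to 57%, 21% or 5%. The document does not support this, because a referral within 12 months is required and the 30-month window serves only the surveillance decision.

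**Conclusion.** The point holds in a narrow form. The written rule lets a control with a letter by month 12 count as a usual-care event when the study's own test led to surveillance. The likely size is between almost none and about two events, assuming that 1% to 5% of controls have such a letter, 25% to 75% accept the test, and 5% to 20% of those tested then enter surveillance. The direction is fixed: towards no difference. One added control event would reverse significance in roughly 3% to 15% of trials at the assumed rates, so it should not be read as likely to decide the result. It deserves correction because the expected counts are small, the error affects one arm only, and the remedy is simple before records are reviewed.

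**What to change.** 1. In Primary outcome and Primary outcome data collection, state for both arms that surveillance counts only when it arises from the index referral made within 12 months, not from a later referral. This removes the non-attender who is referred again.
2. Record the date of any study VCTE or biomarker test in controls.
3. Report a sensitivity analysis, by date alone, that does not count control surveillance decisions made after a study test. This covers the control whose index referral was still open when the study result arrived. It may drop a few genuine usual-care events and so favours screening; say so and present it as a bound.
4. Reconcile the Arm 2 text with the Patient and public involvement text on when the offer is made relative to closure of the participant's primary outcome record.

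Using dates avoids asking an unblinded team to judge, in one arm only, whether a decision rested on the study test, which would weaken an outcome meant to be objective. The cost is one sentence in the outcome definition, one date field and one extra analysis, plus reading some letters to see which referral led to surveillance. The offer to controls is kept, and nobody needs to be recontacted for outcome data.
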